### Adverse event reporting and harms {22}

Adverse event (AE) reporting is managed on the trial database and reported to the trial team within SCTU.

Of AEs deemed to be non-serious, only those considered related to the trial interventions (rather than solely related to the appendicitis itself) need to be recorded. However, the following expected AEs do not require recording if they are not serious: (i) fever, (ii) vomiting, (iii) diarrhoea and (iv) non-recurrent abdominal pain.

For this trial, only serious adverse events (SAEs) deemed related to the trial intervention and not in the list of exceptions or list of expected AEs need to be reported to the SCTU as SAEs. The following SAEs do not require reporting to SCTU: (i) prolonged hospital stay due to treatment of appendicitis; (ii) re-admission to hospital for complication of either treatment and/or appendicitis; (iii) admission to hospital for treatment of recurrent appendicitis; (iv) hospitalisations for elective treatment of a pre-existing condition; and (v) hospitalisations for an unrelated condition. These events (if deemed trial-related) should be reported to SCTU as AEs.

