### Intervention description {11a}

#### Non-operative treatment group

This treatment pathway will comprise (i) fluid resuscitation, (ii) a minimum of 24-h intravenous antibiotics (determined by local hospital standard antibiotics for appendicitis, as per our feasibility study), (iii) analgesia and (iv) regular clinical review to detect symptoms and signs of significant clinical deterioration including, but not limited to, increasing fever, increasing tachycardia and increasing pain/tenderness. In our feasibility study [5, 13–19], we recommended a minimum period of being ‘nil-by-mouth’ but learnt from experience that this was unnecessary and deterred some children from participating, therefore this requirement has been removed for this RCT.

Once children have received minimum 24-h intravenous antibiotics, have been afebrile for 24 h and are tolerating oral intake, they will be converted to oral antibiotics (co-amoxiclav as per standard practice). Once discharge criteria are met (see below), they will be discharged. In total, children in the intervention group will receive a course of 10 days antibiotics following randomisation. Children who receive non-operative treatment will not be offered appendicectomy, but they and their parents will be counselled about the risk of recurrence and appropriate action to take. Children who require appendicectomy for failure of non-operative treatment during the initial admission will be treated post-operatively according to a standardised treatment regime already in use at participating institutions, and identical to that to be used in children in the appendicectomy group.

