#### Appendicectomy group

Children allocated to appendicectomy group will undergo urgent appendicectomy according to current treatment pathways at participating centres. The procedure may be performed by a suitably experienced trainee (as is routine current practice) or a consultant. The procedure may be performed open or laparoscopically at the discretion of the clinical team according to their current practice (in our feasibility study, open appendicectomy was a rare event).

It is recommended to take a peritoneal microbiology swab at the time the peritoneum is first opened and any peritoneal fluid sent for microbiological culture. Participants will receive intravenous antibiotics from the time of randomisation and be treated post-operatively with intravenous antibiotics (according to existing treatment pathways already in use at participating centres). Typically, children with uncomplicated acute appendicitis or a macroscopically normal appendix will receive no further antibiotics. If unexpectedly a perforated appendix is discovered at surgery (defined as a faecalith or faecal matter within the peritoneal cavity or visualisation of a hole in the appendix) [21], then intravenous antibiotics will be continued for a minimum of 3 days, with a minimum total course of antibiotics of 5 days (intravenous and oral). It is not possible to completely ‘protocolise’ the duration of antibiotic therapy due to anticipated variation in response to treatment. Children with perforated appendix will remain in the RCT.

The type of antibiotics initially used will be according to current standard local hospital policy. Any child failing to respond to these first line antibiotics will be treated as is clinically appropriate with a longer course of antibiotics, or a change in antibiotic therapy with choice of antibiotic determined by intra-operative swab or fluid culture. Post-operatively, children with uncomplicated acute appendicitis or a normal appendix will not routinely have a nasogastric tube, nor a urinary catheter; they will receive oral intake as tolerated after surgery.

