### Participant timeline {13}

Table 4 shows the participant timeline for patient’s observations and procedures.

**Table 4 Tab4:** Schedule of observations and procedures

**Visit/time point (all measured from randomisation:**	**Baseline/randomisation**	**Treatment**	**Dis-charge**	**1 week**^**a**^ (+ 3 days)	**2 weeks**^**a**^ (+ 3 days)	**3 weeks**^**a**^ (+ 3 days)	**4 weeks**^**a**^ (+ 3 days)	**6 weeks** (− 1 week/+ 2 weeks)	**4 months**^**a**^ (− 1 week/+ 2 weeks)	**8 months**^**a**^ (− 1 week/+ 2 weeks)	**12 months**^**a**^ (− 1 week/+ 2 weeks)
Informed consent	**X**										
Eligibility evaluation	**X**										
Medical history	**X**										
Diagnostic tests as per standard practice (blood test—Total WBC/CRP/Neutrophil, CT scan, Ultrasound)	**X**										
Pregnancy test^b^	**X**										
Physical exam (abdomen exam)								**X**			
Vital signs (temperature)	**X**										
Randomisation	**X**										
Appendicectomy (arm B only)		**X**									
IV antibiotics (arm A only)		**X**									
Doctor/healthcare professional assessment	**X**							**X**			
Histology following surgery								**X**	**X**	**X**	**X**
Discharge assessment			**X**								
Adverse Events	**X**		**X**	**X**	**X**	**X**	**X**	**X**	**X**	**X**	**X**
Health economics—resource use	**X**		**X**	**X**	**X**	**X**	**X**	**X**	**X**	**X**	**X**
CHU-9D	**X**			**X**	**X**	**X**	**X**	**X**	**X**	**X**	**X**
Patient data collected on app				**X**	**X**	**X**	**X**				
Client service receipt inventory (CSRI)								**X**	**X**	**X**	**X**
Recurrence								**X**	**X**	**X**	**X**
Complication requiring intervention under general anaesthesia	**x**							**x**	**x**	**x**	**x**

^a^To be collected remotely via phone call and/or app

Data collected on app:

▪ Pain relief taken Y/N

▪ CHU 9D proxy and self-report where appropriate

▪ Antibiotics taken Y/N

▪ Able to do normal daily activities Y/N

▪ Attended school Y/N

▪ Able to do full activities Y/N

▪ Parents missed work Y/N

▪ The last week have you had any contact with a health care professional(s) for your child’s appendicitis? Y/N

^b^Only for those of childbearing potential

NB: The Participant/legal representative is free to withdraw consent at any time without providing a reason. When withdrawn, the participant will continue to receive standard clinical care. Follow up data will continue to be collected (unless the participant/legal representative has specifically stated that they do not want this to happen)

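### Non-serious diarrhoea and vomiting need not be recorded even when related to treatment, so the adverse-event table cannot compare them between arms with different antibiotic exposure

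*Protocol article*

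**What the plan says.** Adverse event reporting and harms {22} sets two successive filters. The first is by relatedness: "Of AEs deemed to be non-serious, only those considered related to the trial interventions (rather than solely related to the appendicitis itself) need to be" entered at all. The next sentence opens with a contrast and adds a second filter by symptom: "the following expected AEs do not require recording if they are not serious: (i) fever, (ii) vomiting, (iii) diarrhoea and (iv) non-recurrent abdominal pain". The second filter has no exception for events judged related to antibiotics or surgery.

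On exposure, the non-operative arm is described thus: "In total, children in the intervention group will receive a course of 10 days antibiotics following randomisation". In the appendicectomy arm, "Participants will receive intravenous antibiotics from the time of randomisation and be treated post-operatively with intravenous antibiotics" under local pathways, and then: "Typically, children with uncomplicated acute appendicitis or a macroscopically normal appendix will receive no further antibiotics". A perforated appendix found at surgery leads to a total course of at least 5 days.

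Table 3 lists adverse events as a secondary outcome and marks them as part of the core outcome set. Statistical methods {20a} says they will be summarised descriptively only. The app list under Table 4 includes "Antibiotics taken Y/N", but no item on diarrhoea or vomiting.

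**The concern.** Events due solely to appendicitis are already removed by the first filter. The symptom exemption therefore acts mainly on events that someone has judged related to treatment, which are the ones a tolerability comparison needs. If diarrhoea or vomiting follows antibiotic use, the arm with the longer course could have more of it, and the plan does not require anyone to write it down.

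The Discussion says that the secondary outcomes are meant to inform shared decisions with families. Several complications of surgery, such as wound infection, other wound complications and intra-abdominal abscess, have their own rows in Table 3. The gastrointestinal symptoms that the plan itself calls expected have none. A reader of the final table could take few or no recorded cases as evidence of good tolerability, when the cases were never systematically sought.

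**Working it through.** **1. Does the exemption reach treatment-related events?** Consider a non-serious episode of diarrhoea in either arm.
- If it is due solely to appendicitis, the first filter already excludes it.
- If it is judged related to an intervention, it passes the first filter, and the second then exempts it.

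So required recording is nil for non-serious diarrhoea and vomiting, whatever the cause.

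**2. Is there another route to the symptom?**
- *Adverse-event row of Table 4:* it is ticked at discharge, weeks 1 to 4, week 6 and months 4, 8 and 12. The occasions exist, but the same recording rule applies at each.
- *Table 3:* no diarrhoea or vomiting outcome.
- *App list (Table 4 notes):* pain relief, CHU-9D, antibiotics taken, normal activities, school, full activities, parents' missed work, and contact with a health care professional. No gastrointestinal item.
- *CHU-9D:* worry, sadness, pain, tiredness, annoyance, schoolwork, sleep, daily routine and joining in activities. None is gastrointestinal.
- *CSRI and readmission:* these record service use, not the symptom.

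**3. Does exposure differ?** Yes, in duration. It is 10 days from randomisation in one arm. In the other it is peri-operative intravenous cover and typically nothing further if uncomplicated. No number of days is stated for the typical control child, so the difference in days cannot be calculated.

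**4. Illustrative size.** The denominator reproduces: 159 / (1 − 0.15) = 187.06, rounded up to 188 per arm, or 376 in total. The documents give no symptom rates, so the rates below are assumptions. Expected cases are 188 × rate. Power is for a two-sided 5% comparison of proportions with 188 per arm, had the symptom been fully recorded.

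| Assumed rate, appendicectomy / non-operative | Expected cases | Power if recorded |
|---|---|---|
| 5% / 10% | 9.4 / 18.8 | 45% |
| 5% / 15% | 9.4 / 28.2 | 90% |
| 10% / 30% | 18.8 / 56.4 | over 99% |

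Formula: power = Φ{[d − 1.96 √(2p̄(1−p̄)/n)] / √[(p₁(1−p₁)+p₂(1−p₂))/n]}. For 5% and 15%, d = 0.10 and p̄ = 0.10. The two square roots are 0.03094 and 0.03051, so the argument is (0.10 − 0.0606)/0.0305 ≈ 1.29 and power ≈ 0.90.

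Across this range a trial of this size could have described, and at the larger differences detected, a contrast that the recording rule leaves out.

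**5. How many children could an amendment still reach?** Recruitment runs from March 2022 to about March 2026, which is 48 months. If it were even, 376 / 48 ≈ 7.8 children enter per month. The article appeared on 4 December 2025, leaving 3 to 4 months: about 23 to 31 children, or 6% to 8% of the total, before allowing time for approval.

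**The case against.** The strongest reply is that this is an open and proportionate choice. Both treatments are routine, adverse events are only described, and these symptoms overlap with appendicitis itself. Their consequences are partly captured in both arms through daily activities, school attendance, parents' work, CHU-9D, health-care contact, the CSRI and readmission. That stands as a reason for a light recording burden. It does not restore the comparison, because those measures carry no label of symptom or cause.

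Several stronger readings are tempting, and the documents do not support them:
- *That the table will favour the non-operative arm.* The exemption applies to both arms. It also covers fever and non-recurrent abdominal pain, which can follow surgery, and vomiting can follow anaesthesia. The net direction over the four symptoms is not established.
- *That the contrast is antibiotics against none.* Control children receive intravenous antibiotics from randomisation, and perforated cases have a minimum course. Non-operative children who fail during the first admission move to the same post-operative regime as the surgical arm.
- *That the trade-off behind the 20% margin cannot be checked.* Sample size {14} rests the wider margin on parental acceptability, avoidance of anaesthesia and of surgical complications, and cost, not on antibiotic tolerability.
- *That serious cases are lost as well.* The exemption from recording is limited to non-serious events. The separate rule that only related events "not in the list of exceptions or list of expected AEs need to be reported to the SCTU as SAEs" governs the reporting route for SAEs, not whether a serious case is recorded at all.
- *That nothing will be recorded.* The wording is permissive, so some sites may enter these events. In an open-label trial this adds a problem, because uneven partial counts cannot be interpreted.

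**Conclusion.** The point holds in a limited form. By a stated rule, non-serious diarrhoea and vomiting fall outside required recording even when related to treatment, and no other listed instrument asks for them. The descriptive adverse-event comparison cannot be relied on to show a between-arm difference in these expected effects, and any partial counts may be inconsistent between sites and arms.

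The case is clearest for diarrhoea. For vomiting the direction is uncertain. The primary outcome, its analysis and the non-inferiority margin are unaffected.

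The conclusion rests on the literal sequence of the two filters, on the stated difference in antibiotic duration, and on one clinical premise that the protocol does not spell out: that antibiotics can cause these symptoms. The protocol calls them expected without saying of which treatment. The size is unknown; the counts in the table above follow only from assumed rates.

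**What to change.** For remaining and future participants, do one of the following, identically in both arms:
- remove diarrhoea and vomiting from the list of symptoms exempt from recording; or
- add one daily yes/no item for each symptom to the existing app or paper card.

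Tabulate the result by arm, and state how many children were enrolled under the new rule. The app starts at discharge, so the second option misses inpatient days; the first does not.

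For participants already past that window, state in the statistical analysis plan and the report that non-serious diarrhoea and vomiting were not systematically collected. Draw no comparative tolerability conclusion from the adverse-event table. With recruitment close to its end, this is the part that reliably protects interpretation.

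The cost is slightly more data entry and an amendment, with data only for children enrolled after the change. The reporting statement costs a sentence. No change to clinical management is involved.

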### Frequency and plans for auditing trial conduct {23}

On receipt of a written request from SCTU, the PI will allow the SCTU direct access to relevant source documentation for verification of data entered onto the eCRF (taking into account data protection regulations). Access should also be given to trial staff and departments (e.g. pharmacy).

The participants’ medical records and other relevant data may also be reviewed by appropriate qualified personnel independent from the SCTU appointed to audit the study, including representatives of the Competent Authority. Details will remain confidential and participants’ names will not be recorded outside the trial site without informed consent.

### Plans for communicating important protocol amendments to relevant parties (e.g., trial participants, ethics committees) {25}

Protocol amendments will be submitted via IRAS for REC/HRA approval where necessary and distributed to all trial sites when these have been approved.

### Dissemination plans {31a}

If they consent to receiving the information, patients or parents will be notified of the results of the trial via the site where they were recruited. The data will be published in a peer-reviewed journal and available in the public domain. Our Study Specific Advisory Group (SSAG) will write a report for participants to ensure the language is appropriate and accessible.

## Discussion

Although there are an increasing number of reports concerning the use of non-operative management of uncomplicated acute appendicitis in children, and a marked increase in the use of this intervention in many jurisdictions during the recent SARS-CoV-2 (COVID-19) pandemic [34, 35], there are very few studies that have undertaken a comparative analysis of the clinical effectiveness of non-operative treatment pathway when compared to appendicectomy. We believe that such comparative analysis is essential to guide future healthcare decisions by clinicians, patients and families.

We acknowledge that Svensson and colleagues [10] have undertaken a small pilot RCT comparing these two treatments, and recently, since the initiation of this trial, two other groups [36, 37] have published findings of larger RCTs (one in Australia, one multinational). Additionally, Minneci and colleagues [11] have reported a large series of children with uncomplicated appendicitis from the USA (*n* = 1068) of whom 370 were treated non-operatively. Using a propensity score matched analysis, they assessed the impact of treatment approach on outcomes, but they did not use randomisation to assign patients to treatment arms. The two larger trials [36, 37], with a similar non-inferiority randomised design to this study, concluded that non-operative treatment was inferior to appendicectomy based on a non-inferiority margin of 20%. Despite this, we believe there is benefit in further comparative effectiveness research in this field for a number of reasons. Firstly, there are subtle differences between our protocol and others—the use of the complicated appendicitis score and a minimum of 24 h of non-operative treatment may both independently increase the likelihood of success of non-operative treatment. Secondly, we believe a further RCT is justified that is specific to the UK setting to provide an assessment of these healthcare technologies in the UK. This is particularly true for a comparative health economic analysis, since the NHS is a unique healthcare economic environment. We also note some differences in the management of appendicitis in the UK compared to other countries that reinforce the rationale for a trial within the UK. Most notably, in the UK, there is only limited use of diagnostic radiology, a relatively high negative appendicectomy rate and limited use of same day discharge after appendicectomy. Since all these factors may influence the comparative effectiveness and cost effectiveness of treatment, we believe a further RCT in the UK is justified. Finally, we note that, although analysis of the primary outcome is important, there is also significant value in understanding the impact of different management strategies on many of the secondary outcomes, since these data are likely to inform shared decision-making models with families going forwards. Understanding these accurately in the UK healthcare setting will result in the most value for NHS patients in the future.

Prior to our feasibility study [5, 13–19], we identified that recruitment may be a challenge for this comparative effectiveness research. We will be reliant on clinical teams (rather than research nurses) to screen potential participants during an emergency admission to hospital, potentially at all hours of the day and all days of the week. In an attempt to optimise recruitment in our feasibility study, we implemented a program of detailed site training, focusing not only on trial processes, but in particular on the way in which site teams communicate with potential participants and their families about the trial [5, 13–19]. Starting with indicative training based on previous research, our communication sub-study alongside the feasibility study [16, 17] allowed us to develop a bespoke training program for site teams specific to this trial. In this phase III RCT, we base initial site training on the findings of our feasibility study [5, 13–19], and also deliver a communication sub-study during the pilot stage of our RCT. We anticipate that this will be of particular importance at sites not involved in the feasibility study.

Selecting the most appropriate primary outcome for any RCT is important. It has an impact on how the trial is interpreted, how likely the findings are to change clinical practice and, in conjunction with the proposed statistical analysis, guides the sample size requirement. During our feasibility study [5, 13–19], we focused on defining the primary outcome for this trial based on feedback from patients, families and surgeons. For this trial, we defined a composite primary outcome, because it encompasses aspects that are important to all these stakeholders in determining whether treatment has been a success. Furthermore, each component of the composite has similar impact on the patient/family, since the occurrence of any will result in unplanned general anaesthesia. This threshold of requiring general anaesthesia is something that patients and families have told us is important to them.

The trial will be analysed using a non-inferiority analysis and a 20% non-inferiority margin. This margin was identified as being acceptable during our feasibility study following discussions with families and surgeons [5, 13–19]. Our non-inferiority approach is supported by the fact that patients and families recognize that non-operative treatment may be slightly less effective (inferior) to appendicectomy, yet they are willing to accept this in order to realise the potential benefits of non-operative treatment. Our feasibility study identified that surgeons too are willing to accept this but their threshold for non-inferiority is more conservative (nearer to zero) than that of patients and families [5, 13–19]. The 20% margin is therefore something of a compromise in order to suit all stakeholders. In addition to reporting the primary outcome for each treatment arm, we will report all components of our primary outcome individually as well as a range of secondary outcomes. We anticipate that this breadth and depth of data will likely be of great interest to patients, families and clinicians when making treatment decisions for each individual patient in the future.

In keeping with the concept that we aim to test the hypothesis that non-operative treatment pathway is non-inferior to appendicectomy, and assuming an existing non-zero difference between them, we will use a one-sided 5% significance level in our primary analysis. We note some controversy in the literature regarding the use of a one- or two-sided 5% significance level in non-inferiority trials and have considered the most suitable approach for this specific trial in some detail. Based on existing data [8–10], the overall direction of effect of the composite primary outcome will be in favour of appendicectomy. The size of that effect will be determined by the contribution of each individual component to generate a composite effect size. At present, there are no published data to suggest that the overall direction of the effect of the composite primary outcome will be in favour of non-operative treatment pathway. That is, based on existing data [8–10], there is no justification for exploring whether non-operative treatment pathway is superior to appendicectomy for this primary outcome. Furthermore, according to the recent review of non-inferiority trials in the UK [38], although it is less common to have a non-zero assumed difference (7/114 reviewed trials), 5/7 hypothesised that the intervention could only be worse, of which 3 used the statistical approach of one-sided 5% significance level [39–41]. On this basis, we intend to use a one-sided 5% significance level in our non-inferiority analysis of the primary outcome.

